## Abstract

**Background:**

Maintaining optimal glycemic control in type 2 diabetes (T2D) is difficult. Telemedicine has the potential to support people with poorly regulated T2D in the achievement of glycemic control, especially if the telemedicine solution includes a telemonitoring component. However, the ideal telemonitoring design for people with T2D remains unclear. Therefore, the aim of this feasibility study is to evaluate the feasibility of two telemonitoring designs for people with non-insulin-dependent T2D with a goal of identifying the optimal telemonitoring intervention for a planned future large-scale randomized controlled trial.

**Method:**

This 3-month randomized feasibility study will be conducted in four municipalities in North Denmark starting in January 2024. There will be 15 participants from each municipality. Two different telemonitoring intervention designs will be tested. One intervention will include self-monitoring of blood glucose (SMBG) combined with sleep and mental health monitoring. The second intervention will include an identical setup but with the addition of blood pressure and activity monitoring. Two municipalities will be allocated to one intervention design, whereas the other two municipalities will be allocated to the second intervention design. Qualitative interviews with participants and clinicians will be conducted to gain insight into their experiences with and acceptance of the intervention designs and trial procedures (e.g., blood sampling and questionnaires). In addition, sources of differences in direct intervention costs between the two alternative interventions will be investigated.

**Discussion:**

Telemonitoring has the potential to support people with diabetes in achieving glycemic control, but the existing evidence is inconsistent, and thus, the optimal design of interventions remains unclear. The results of this feasibility study are expected to produce relevant information about telemonitoring designs for people with T2D and help guide the design of future studies. A well-tested telemonitoring design is essential to ensure the quality of telemedicine initiatives, with goals of user acceptance and improved patient outcomes.

**Trial registration:**

ClinicalTrials.gov, ID: NCT06134934. Registered November 1, 2023. The feasibility trial has been approved (N-20230026) by the North Denmark Region Committee on Health Research Ethics (June 5, 2023).

**Supplementary Information:**

The online version contains supplementary material available at 10.1186/s40814-024-01509-0.

## Background

Diabetes represents a major health challenge worldwide. In 2017, it was estimated that 8.4% (451 million) of the adult global population had diabetes. The prevalence is expected to increase to approximately 9.9% (693 million) by 2045, for instance due to an increase in obesity and unhealthy diets [1–4]. Type 2 diabetes (T2D) accounts for approximately 90–95% of diabetes cases [5, 6].

To prevent and control diabetes-related complications, it is crucial to maintain glycemic control [7, 8]. However, optimal glycemic control is often difficult to maintain [7, 9], and less than 50% of people with diabetes reach their goal of glycemic control [10, 11]. The main challenge is that people with diabetes are highly responsible for disease management outside of hospital settings. The person with diabetes is required to perform complex care activities and make numerous daily decisions regarding self-management [9]. Therefore, alternative approaches in diabetes care are needed to support people with diabetes in achieving the desired treatment goals. In several studies, telemedicine has led to positive results in supporting people with diabetes [12–23]. Telemedicine solutions involve the transfer of information or data between a health care professional (HCP) and patients over a geographical distance and the provision of tailored feedback [24]. Telemedicine solutions vary [25, 26], ranging from simple short message service reminders to more complex telemonitoring solutions where the patient performs selected measurements at home and transfers their data to monitoring HCPs [16, 17, 20, 27–31]. Thus, telemedicine has a large potential to support people with diabetes in achieving glycemic control. Moreover, for those who are unable to travel to a health care clinic, telemedicine has the potential to increase access and provide better health outcomes [32].

In a comprehensive 2017 review, it was reported that telemedicine for people with diabetes is a safe way to provide support for self-care [33]. Several other evaluations of telemedicine solutions have shown varying results but with a positive trend considering glycemic control [15, 26, 34–37]. A review and meta-analysis by Faruque et al. from 2017 showed an improvement in glycated hemoglobin (HbA1c) in people with T2D who used telemedicine as a supplement to regular care [26]. Furthermore, in 2021 Hangaard et al. performed a systematic review, meta-analysis, and meta-regression focusing on T2D; they concluded that telemedicine may serve as a valuable supplement to usual care, especially if the solution includes a telemonitoring component, and that patients with poor glycemic control may benefit more from telemedicine than their well-regulated counterparts [16]. However, the ideal telemonitoring setup for T2D remains to be determined [16].

Telemonitoring interventions may have the potential to postpone the start time for insulin treatment and reduce the risk of diabetes-related complications in people with T2D if they focus on diabetes self-management education components. Such interventions could potentially provide the foundation for people with T2D to navigate the daily self-management and care activities related to diabetes [38, 39]. Diabetes self-management education components are the elements that facilitate skills, knowledge, and ability necessary for diabetes self-care [39]. Such components are the first step in T2D management and have been shown to improve health outcomes in people with diabetes [38, 40–42]. Different telemonitoring approaches focused on diabetes self-management education could be relevant in supporting people with non-insulin-dependent T2D. One essential approach is self-monitoring of blood glucose (SMBG), as it provides instant feedback on glycemic values rather than waiting for the next HbA1c [8]. Another relevant approach is monitoring sleep. Sleep disorders are prevalent in T2D and are associated with impaired glucose control and an increased risk of developing diabetes complications [43, 44]. Conversely, diabetes and its complications are associated with poor sleep quality, insomnia, and higher use of sleep medications [45, 46]. An increased awareness of proper sleep is important, as sufficient sleep can prevent diabetes progression [43, 44]. Thus, improvement of sleep could aid the treatment and course of T2D [44]. A third approach is monitoring of mental health, as people with diabetes are known to have more psychological problems compared to the general population associated with increased health care costs [47, 48]. In this regard, telemedicine specifically designed to help people with diabetes understand and better manage mental health symptoms has been shown to decrease anxiety, depression, and stress in people with diabetes [48]. A fourth relevant approach is monitoring blood pressure. Blood pressure levels are higher among people with T2D, and increased values are a well-established risk factor for cardiovascular events [49–51]. Thus, lowering blood pressure in people with T2D is associated with improved clinical outcomes and reduced mortality [51]. Finally, a fifth relevant telemonitoring approach is monitoring and follow-up on physical activity. Thus, studies show that physical activity and reducing sedentary behavior are essential for maintaining glycemic control in people with T2D [52, 53].

## Objectives

The main objective of this study is to evaluate the feasibility of different telemonitoring intervention designs for people with non-insulin-dependent T2D as a supplement to usual care (i.e., regular diabetes controls with the patient’s general practitioner) with the goal of identifying the most suitable design for a planned future large-scale randomized controlled trial. The study is designed to build on a delimited set of intervention components of presumed greatest importance to people with non-insulin-dependent T2D to help prioritize the components in the planned randomized controlled trial.

A secondary objective is to gain useful information for the design of the planned future randomized controlled trial. Apart from evaluating and identifying the most suitable intervention design, the study is expected to provide relevant information on the target group, sample size estimation, recruitment opportunities and challenges, suitable outcome measures, and follow-up rates [54]. Furthermore, the feasibility study is intended to help clarify whether the target group has specific wishes and requirements for a future telemedicine solution as well as whether there is any aspect of the group's social environment that requires special attention [55].

## Methods

This protocol paper is reported in accordance with an adjusted version of the SPIRIT2013 Statement: Defining standard protocol items for clinical trials [56]. The Standard Protocol Items: Recommendations for Interventional Trials (SPIRIT) checklist is available in Additional file 1. The adjustments made include the suggestions by Lehana Thabane & Gillian Lancaster in “A guide to the reporting of protocols of pilot and feasibility trials” [57], a guide that includes items from the CONSORT 2010 statement: extension to randomized pilot and feasibility trials [58].

### Study design and setting

The trial is a feasibility study with a trial period of 3 months. The trial will be conducted as a randomized cluster study in four municipalities in North Denmark (Hjørring, Morsø, Jammerbugt, and Rebild). Two different telemonitoring designs will be tested to identify the most suitable telemonitoring intervention for a future randomized controlled trial on a large scale. Two municipalities will test one intervention design (group 1), while the other two municipalities will test the second intervention design (group 2). The overall trial design is illustrated in Fig. 1.

**Fig. 1 Fig1:**
[figure not shown]
Feasibility study design

The municipalities will be randomized using a drawing of envelopes approach. The drawing will be performed in groups based on the setting of the respective municipalities to ensure that each intervention design will be tested in a health care center as well as in a home health care setting.

All participants will be provided with a telemonitoring account (OpenTeleHealth North account), a blood glucose monitoring kit, and a tablet (unless the participant prefers to use his or her own tablet or smartphone) at trial initiation. The participants will monitor sleep and mental health status through questions implemented in the telemonitoring system. Sleep will be monitored using sleep item questions from a Danish patient-reported outcome (PRO) questionnaire for T2D, while mental health will be monitored through the World Health Organization Five Well-being Index (WHO-5) questionnaire. In addition, the participants in group 1 will be provided with a blood pressure monitor and an activity tracker.

All participants will be trained in using the provided technologies at trial initiation. They will use the distributed devices continuously at home to collect, log, and transfer data to the municipality nurse for the entire trial duration. The municipality nurses will monitor the participants’ data weekly using the telemonitoring system. They will contact the participants by phone, video, or text message at least every other week during the first 6 weeks of the trial. For the final 6 weeks, the frequency of contacts will be tailored based on the needs of the individual participant. Hence, participants may be contacted more frequently than every other week if it is considered relevant by the monitoring municipality nurse. All calls to participants will be recorded in their respective electronic care journals as a part of mandatory registration for the municipality nurse. Participants will be informed that they remain responsible for monitoring and managing their blood glucose levels despite telemonitoring. Furthermore, since the intervention should be seen as a supplement to usual care, the participants are informed that they should continue usual care (diabetes-related visits and controls) with their general practitioner during the trial.

At the end of the trial, participants from both intervention groups will have a final visit with the monitoring municipality nurse. The visit can take place either at the local municipality trial site or at the participant’s home.

Due to the nature of the trial, it will not be possible to blind participants, HCPs, or researchers.

### Outcomes and data collection

The outcomes are used to explore the two different intervention designs to identify the best possible design for a future randomized controlled trial and not to define the statistical or clinical effectiveness of the two interventions. The SPIRIT figure (Fig. 2) provides an overview of the time schedule for enrolment, interventions, and assessments as anticipated in the feasibility trial.

**Fig. 2 Fig2:**
[figure not shown]
SPIRIT figure. Participant timeline with schedule of enrolment, intervention(s), and assessment time points for both intervention groups

#### Demographics

Patient demographics will be obtained at trial initiation, including age (civil registration number), sex, height, weight, blood pressure, civil status, educational level, duration of diabetes, diabetes complications, concomitant medications, concomitant illness, and health-related habits. In addition, baseline HbA1c and lipid values will be used to characterize the participants (blood sampling procedures are explained in the “ Feasibility of the blood sampling schedule” section).

#### Recruitment process

The recruitment assessment will include the following:Number and proportion of people agreeing to receive a participant information letter about the trialNumber and proportion of eligible participants who agree to participatePotential inequalities regarding recruitment feasibility will be assessed by comparing demographic data on age, sex, ethnicity, educational level, municipality, setting (health care center versus home health care setting), and HbA1c (baseline)

#### Retention

The retention assessment will include the following:Number and proportion of participants withdrawing from the trialTimepoint(s) for withdrawalReasons for discontinuation of the trialPotential inequalities regarding retention assessed by comparing demographic data on age, sex, ethnicity, educational level, municipality, setting (health care center versus home health care setting), and HbA1c (baseline)

#### Feasibility of questionnaires

Another outcome is to evaluate the use of selected questionnaires in the intervention designs based on response rates. This will be done to assess their suitability for the patient group and the future large-scale randomized controlled trial. Therefore, the participants will be encouraged to answer the following four questionnaires at baseline and at the end of the trial approximately three months after inclusion:Diabetes-related quality of life: The Problem Areas in Diabetes Questionnaire (PAID5)Quality of Life: The Short Form 12 Questionnaire (SF-12v2)Well-being: The World Health Organization Five Well-being Index (WHO-5)Knowledge, skills, and confidence in managing health: The Patient Activation Measure questionnaire (PAM)

#### Feasibility of the blood sampling schedule

HbA1c will be collected at baseline and 3, 6, and 12 months after inclusion. In addition, lipids will be collected at baseline together with HbA1c. Blood samples will be drawn to explore the following:If there are any analysis challenges or uncertaintiesAdherence among participants to the blood sampling schedule: number and proportion of the participants who completes the blood sampling at baseline, 3 months, 6 months, and 12 months

All blood samples will be drawn by staff at the participant’s general practitioner. The samples will be analyzed as soon as possible after extraction at Aalborg University Hospital or at the North Denmark Regional Hospital but no later than 5 days after extraction, after which the samples will be destroyed. Data on HbA1c at 6 and 12 months after inclusion will be based on blood samples collected as part of regular clinical practice.

#### Experiences with and acceptability of intervention design(s)

Following the 3-month intervention period, individual semi-structured qualitative interviews will be conducted with selected participants and HCPs to gain deeper insight into the participants’ and HCPs’ experiences and acceptability with the two different telemonitoring intervention designs (cf. the “ Study design and setting” section) and the trial procedures. The interviews will, for example, include questions concerning the following information:How they experience and feel about the intervention and the telemonitoring equipment and designHow they assess the burden of being involved in the interventionIf they have any ethical concerns about participating in the intervention

In addition, the interviews will cover the following information:Recruitment opportunities and challengesPerspectives on retention problemsPerspectives on the use of selected questionnaires in the intervention designs and the use of the PRO (sleep items) and the WHO-5 questions as part of the telemonitoring intervention during the trial (cf. section “ Study design and setting”)If the planned timepoints for blood sampling are suitable and meaningful for the future large-scale randomized controlled trial considering potential challenges in relation to social factors, clinical workflows, processes, etc.

#### Intervention costs

Using interviews with HCPs and administrative personnel, a particular focus throughout the feasibility study is to investigate sources of direct and indirect intervention costs for the two alternative intervention designs across the region, the included municipalities, and general practitioners. Study-induced costs will be excluded (e.g., time spent distributing study questionnaires and other activities not included when implementing the potential interventions in routine practice). Potential direct resource categories are in principle uncertain but could include equipment and time spent on monitoring, time spent training patients in using the equipment, additional training for community nurses, and additional time spent by general practitioners in running the offer. Indirect costs could include software licensing, technical support, swapping defect equipment, IT maintenance, server allocation space, etc.

#### Eligibility criteria

The inclusion criteria for participating in the feasibility study will be as follows:Adults ≥ 18 yearsPoorly controlled T2D, i.e., HbA1c > 58 mmol/molDiagnosis of T2D for at least 12 monthsGeneral practitioner responsible for diabetes treatmentResidence in Hjørring, Morsø, Jammerbugt, or Rebild municipalityAbility and willingness to use a smartphone/tablet along with the other devices to be used in the trialSigned informed consentAbility to understand and read Danish

The exclusion criteria will be as follows:Pregnancy or breastfeedingInsulin treatmentPrednisolone treatmentSevere diabetes complications such as severe neuropathy or nephropathy (dialysis treatment)Participation in diabetes rehabilitation courses and in other intervention trialsTerms that, in the opinion of the sub-investigator or investigator, render the participant unfit to conduct the trial, including lack of understanding of the trial or lack of physical or cognitive ability to participate.

### Sample size

Power calculation will not be conducted, as hypothesis testing is inappropriate in feasibility studies and therefore not an objective of this trial [54]. Instead, the sample size will be based on recommendations in the literature. A general rule is a sample size of 30 patients or greater in pilot studies [59]. Furthermore, 12 [60] to 50 [61] participants per arm have been suggested. Based on these recommendations, 60 participants will be included in the feasibility study, with 30 participants undergoing each intervention design.

### Recruitment and ethical considerations

Eligible people with non-insulin-dependent T2D will be recruited through general practitioners (or HCPs from the municipalities can send an inquiry to general practice) in the four municipalities in connection with diabetes consultations. The general practitioners will briefly inform the participant about the trial, hand out a participant information letter to interested patients, and refer them electronically to the municipality project nurses for potential inclusion. The potential participants will subsequently be called in for an information meeting with the possibility of a companion. This will be described in the participant information letter, which will also explain the purpose and design of the trial. During this meeting, the potential participant will be given in-depth information about the trial and will have the opportunity to ask questions. Moreover, attempts will be made to determine whether the potential participant is motivated and suited to participate in the telemonitoring trial. The information meeting will take place in a closed room at one of the municipality sites or in the participant’s home, where the conversation can take place undisturbed. The information meeting will be conducted by a municipality nurse (authorized by the primary investigator to perform the task) from the project team with the necessary professional knowledge. During the meeting, the participant will be made aware of her or his right to a reflection period of at least 24 h prior to giving informed consent and that the consent can be withdrawn at any time and without justification. Only when informed consent has been obtained with the signature of both the participant and the municipality nurse will the trial begin.

The recruitment of participants for the interviews will be conducted continuously due to ongoing inclusion of eligible participants throughout the whole trail period. Toward the end of the three months trail period, selected participants will be contacted by one of the researchers to receive information about the interview and asked about interest in possible participation. To ensure broad perspectives, a maximum variation sampling strategy will be sought to ensure that the interviews cover perspectives from both telemonitoring designs and both settings (i.e., health care center and home health care setting). Moreover, attempts will be made to include participants of varying genders and age groups.

Recruitment of HCPs for the interviews will be conducted towards the end of the entire trail period. It will be aspired to recruit one HCP for each municipality to ensure a broad perspective across municipality nurses. However, the recruitment process will depend upon organizational and logistical feasibility such as resources and work schedules.

The trial will be terminated in the event of any serious adverse events related to the trial as considered by the primary investigator. Furthermore, the trial will be stopped for the individual participant if severe hypoglycemia (low blood glucose; severe defined as levels ≤ 54 mg/dL), ketoacidosis (when ketone acids are build up to potentially dangerous levels in the body), or severe hyperglycemia (high blood glucose; severe defined as levels ≥ 180 mg/dl) is recorded and determined by the primary investigator to be related to the trial. However, the risk of such events is low since participants on insulin therapy will be excluded. If the trial is stopped for the individual participant or if a participant requests to withdraw from the trial, a subsequent final meeting with a municipality nurse is offered. At this visit, any questions from the participant will be answered.

The trial will be carried out in accordance with the Helsinki Declaration [62] and the principles of good clinical practice (GCP) [63]. Furthermore, the North Denmark Region Committee on Health Research Ethics approved the trial (Project ID: N-20230026).

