### Analysis

Descriptive statistics will be used to present baseline demographics. Continuous data will be summarized using the mean and standard deviation, while categorical data will be presented as percentages.

The data collected from the qualitative interviews will be analyzed through inductive thematic analysis to identify central themes.

The extent of missing data from the participants throughout the trial period, response rate for the questionnaires, and number of completed blood samplings will be collected and presented using descriptive statistics. The data will be used to evaluate acceptability and adherence among the participants to the two intervention designs.

The intervention design for a future randomized controlled trial will be determined by:Comparison of the quantitative results (recruitment, retention, and intervention costs) derived from the two intervention designs. If there is no notable difference in the quantitative results between the two intervention designs, the design with the least number of components will immediately be preferred to ensure the most favorable solution for a larger populationAn overall assessment, incorporating the quantitative results and findings from the qualitative interviews (with participants and HCPs), through dialogue between the researchers and involved personnel from the North Denmark Region, municipalities, and general practitioners

As already stated, no sample size calculation will be performed since the present study is a feasibility trial. However, the results from the trial are expected to provide useful information on sample size calculation for the future randomized controlled trial regarding drop-out estimation.

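### The recruitment proportion is taken among eligible people, yet eligibility already includes device willingness and signed consent, so the proportion overstates uptake and can hide a difference between the designs

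*Protocol article*

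**What the plan says.** Allocation is by municipality: "The trial will be conducted as a randomized cluster study in four municipalities in North Denmark" (Study design and setting). The same section adds that "The municipalities will be randomized using a drawing of envelopes approach", that "the participants in group 1 will be provided with a blood pressure monitor and an activity tracker", and that "it will not be possible to blind participants, HCPs, or researchers".

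Four provisions then bear on the recruitment figure:

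- **Recruitment process** lists two proportions: people who accept the information letter, and eligible people who go on to agree.
- **Eligibility criteria** includes, among the inclusion criteria, being able and prepared to use a phone or tablet and the trial's other devices, and having signed consent.
- **Recruitment and ethical considerations** describes an information meeting held by a project nurse before consent, at which "attempts will be made to determine whether the potential participant is motivated and suited to participate in the telemonitoring trial".
- **Analysis** makes the first step in choosing the design a "Comparison of the quantitative results (recruitment, retention, and intervention costs) derived from the two intervention designs". If no notable difference is seen, the design with fewer components is preferred. An overall assessment that includes the interviews also enters.

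Retention is counted among participants (Retention).

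**The concern.** The designs differ in device burden: group 1 has two devices more than group 2. Unwillingness to take on those devices is therefore one of the main things a recruitment comparison should show. If unwillingness makes a person ineligible, and the proportion is taken among the eligible, that information is removed before it is counted.

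Two uses of the figure are affected. Recruitment is one of the three quantitative inputs to the design choice. The Objectives section also expects the study to inform recruitment and follow-up rates for the large trial, and an overstated uptake would lead to too few referrals being planned.

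**Working it through.** **The plan's own figures.** The abstract says "There will be 15 participants from each municipality": 4 × 15 = 60 in total and 2 × 15 = 30 per design. This agrees with the Sample size section ("60 participants will be included in the feasibility study, with 30 participants undergoing each intervention design"). If the targets are met, the number enrolled is the same in both designs by construction, so the information on recruitment lies in the denominator.

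**The literal reading.** If eligible means that every listed criterion is met, everyone in the denominator has already signed consent, and enrolled ÷ eligible = 100% in both designs. The measure then carries no information.

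**The reading without consent, keeping willingness.** The protocol gives no rates, so these inputs are assumptions: agreement among the eligible is a = 60% in both designs; a share u of the people referred in group 1 is unwilling to use the extra devices; nobody is unwilling in group 2.

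Reported proportion = a. Uptake among those referred = a × (1 − u). Referrals needed for 15 enrolled = 15 ÷ uptake, rounded up.

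| u in group 1 | Reported, group 1 v group 2 | Uptake in group 1 | Hidden gap | Referrals per 15, group 1 v group 2 |
|---|---|---|---|---|
| 10% | 60% v 60% | 0.60 × 0.90 = 54% | 6 points | 28 v 25 |
| 20% | 60% v 60% | 0.60 × 0.80 = 48% | 12 points | 32 v 25 |
| 30% | 60% v 60% | 0.60 × 0.70 = 42% | 18 points | 36 v 25 |

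This gap between designs arises if willingness is judged against the allocated devices. If the criterion covers all trial devices in all four municipalities, the same 6 to 18 points are an overstatement of uptake in both designs, and no gap is hidden.

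**Coverage of the other proportion.** Accepting the letter follows a brief mention by the general practitioner. The in-depth information and the nurse's screen come later. Neither proportion covers losses between the letter and eligibility.

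**Retention, only if willingness is judged against allocated devices.** Let s be the share of people willing to use the lighter design who would not accept the heavier one. In group 1 they are screened out; in group 2 they enrol. The gain in observed group 1 retention is s × (retention in group 1 of people willing for both designs − retention the others would have had there). On assumed values:

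- Smallest case: 0.10 × (0.85 − 0.60) = 2.5 points, about 1 of 30.
- Largest case: 0.40 × (0.90 − 0.50) = 16 points, about 5 of 30.
- A case where the sign changes, with s = 30%: observed group 1 is 85%; group 2 is 0.70 × 0.90 + 0.30 × 0.70 = 84%, so the difference is +1 point. Unselected group 1 would be 0.70 × 0.85 + 0.30 × 0.50 = 74.5%, a difference of −9.5 points.

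In other assumed cases the heavier design still looks worse. For scale, the 95% half-width of a retention difference with 30 per design is 1.96 × √(2p(1 − p)/30). This is 15 points at p = 0.90 and 20 points at p = 0.80, before any allowance for clustering.

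**The case against.** The strongest reply is that eligible cannot mean every listed criterion, because the measure would then be 100% by construction. Recruitment and ethical considerations itself calls people eligible when they are still to be recruited through general practitioners, before the nurse's meeting. On that usage a referred person who declines because of the devices is a refusal inside the denominator. This stands as a possible intention. It also shows that the article uses the word in two senses, and the recruitment proportion does not say which one applies.

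Other replies have weight. The willingness criterion speaks of the trial's devices, not those of the municipality's own design, so different eligibility by group is only one reading. Recruitment after the draw is the natural reading given ongoing inclusion, but the order is not stated. The motivation screen is common to both designs. If the large trial enrols only willing people, retention among such people is relevant to it. Recruitment and retention are to be compared across demographic factors including municipality, which covers part of a comparison by design. Interviews and costs also inform the choice.

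A reader might infer that the plan is tilted towards the heavier design. The documents do not support that for recruitment. Lower uptake that is masked looks like a tie, and the Analysis section gives ties to the design with fewer components. None of the assumed recruitment scenarios made the heavier design look better. Only retention could work in its favour, and only on the allocated-devices reading.

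**Conclusion.** The point holds as a defect in a stated denominator. With willingness and consent inside eligibility and a motivation screen before consent, the recruitment proportion overstates uptake, and at the literal limit it is 100%. With an assumed 60% agreement and 10% to 30% unwilling, 6 to 18 points are lost from view. They are a hidden difference between designs if willingness refers to allocated devices, and an overstatement in both designs if it refers to all devices.

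The retention effect is secondary and conditional. It is 2.5 to 16 points on assumed rates, zero if nobody is screened out, and mostly within the sampling error of 30 per design. It should not be read as showing that the heavier design will be chosen. The change is worth making because the figures feed both the design choice and the planning of the large trial, and because it costs almost nothing.

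**What to change.** - Define the recruitment proportion as people enrolled divided by all referred people who meet the clinical criteria. Leave willingness, motivation, suitability and consent out of the denominator.
- Report non-recruitment by reason (unwilling to use the devices, judged not motivated or suited, declined) and by design.
- State whether the willingness criterion covers all trial devices or only those of the municipality's own design.
- Show baseline characteristics by design beside the retention comparison.

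The cost is one definition, one clarifying sentence and a reason field on the nurses' screening log. Reported recruitment proportions will be lower. The sample size, the visits and the interventions do not change.
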